### Data collection, follow-up and outcomes

#### Data collection

In addition to clinical and behavioral outcomes, baseline data are collected to describe the characteristics of study participants (providers and patients) and compare these characteristics between intervention groups assigned by randomization. These data include: self-reported provider demographic data (age, gender, years of experience, specialty, preferred language), provider perception of practice team cohesiveness, self-reported patient socio-demographic data (age, gender, race/ethnicity, social support, education, income, health literacy, zip code, insurance status), co-morbid conditions (diabetes, hypertension, cardiovascular disease), food insecurity, and health literacy (Table 1).

**Table 1 Tab1:** Kidney Awareness Registry and Education (KARE) study variables and outcomes

KARE Study data collection	Method of ascertainment	Baseline	Mid-point	Study end
Primary care providers				
*Demographic data*				
Age, gender, years of experience, language	Survey	+		
*Behavioral data*				
Awareness/ability to identify CKD	questionnaire [35]	+		+
Self-efficacy towards CKD management	questionnaire	+		+
Comfort communicating with patients about CKD	Communication Assessment Tool [36]	+		+
Prescription of ACEi or ARB, albuminuria quantification, nephrology referral	Medical record	+		+
Patients				
*Demographic data*				
Age, gender, race/ethnicity, social support, income, education, zip code, preferred language, insurance status	Survey	+		
Food insecurity, health literacy	Screening questions	+		
*Clinical data*				
BP, Height, Weight, UACR,	Measured by study team	+		+
eGFR, metabolic bone disease parameters, glycosylated hemoglobin	Medical record	+		+
Co-morbid conditions	Medical record	+		+
Referrals, emergency department visits, hospitalizations	Medical record	+		+
Current medications	Medical record and study team	+	+	+
Quality of life, functional status	SF-12 instrument [37]	+		+
*Behavioral data*				
CKD awareness	Survey	+	+	+
Participation in healthy behaviors	BRFSS questionnaire [40]	+	+	+
Self-efficacy for self-management	Stanford self-efficacy tool [39]	+	+	+
Medication Adherence	Morisky Medication Adherence Scale [38]	+	+	+
Communication with providers	Lorig Communication tool [39]	+	+	+

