#### Clinical outcomes

The primary outcomes are changes in systolic BP and proportion of patients with BP control (<140/90 mmHg) after one year. The study team will measure BP using an Omron digital blood pressure monitor model HEM-907X during baseline and 12-month study visits. Per study protocol and American Heart Association guidelines, study personnel will obtain 3 BP measures in the right arm after the participant has been sitting quietly for 5 min [34]. An average of the 3 measures is recorded. Secondary clinical outcomes include: changes in urine albuminuria and weight obtained during by the study team, as well changes in eGFR, laboratory measures of metabolic bone disease (serum calcium, phosphorous, 25-OH Vitamin D and parathyroid hormone) and glycosylated hemoglobin among participants with diabetes, all ascertained through the EMR.

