### Data analysis

Evaluation of the individual effectiveness of each intervention, as well as their additive impact, will be performed with intention to treat analyses using generalized estimating equations adjusting for patient age, clinic and preferred language, with robust standard errors to account for clustering by provider and repeated patient measures within provider. If significant differences in baseline characteristics (i.e., age, diabetes status) are found among subjects in each study arm, analyses will be adjusted for these differences using multi-variable linear regression. Additional analyses will look for evidence of effect modification by primary language and CKD severity.

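### Significance tests on baseline differences decide which extra covariates enter the analysis, through a linear regression whose relation to the planned GEE is not stated

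*Protocol article*

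**What the plan says.** The Data analysis section of the protocol article has two steps. The first applies to every analysis of the two interventions: "generalized estimating equations adjusting for patient age, clinic and preferred language". The standard errors in this model are robust ones, meant to allow for patients sharing a provider and for repeated measurements. These covariates do not depend on what the data show.

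The second step is conditional: "If significant differences in baseline characteristics (i.e., age, diabetes status) are found among subjects in each study arm, analyses will be adjusted". The method named for that adjustment is a linear regression with several covariates. The step gives no significance level and no closed list beyond the two variables in brackets. It does not mention clustering and does not say how it relates to the GEE.

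The Data collection section says that one purpose of the baseline data is to "compare these characteristics between intervention groups assigned by randomization". The Clinical outcomes section defines one continuous and one binary primary outcome: "The primary outcomes are changes in systolic BP and proportion of patients with BP control (<140/90 mmHg) after one year".

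**The concern.** After correct randomisation, a baseline difference between arms is due to chance. Its p-value says nothing about how strongly the variable predicts blood pressure, and that is what makes adjustment worthwhile. A strong predictor that happens to be balanced would be left out, and a weak one that happens to be imbalanced would go in. The final covariate set is then known only after the data have been seen.

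The wording of the conditional step adds three problems:

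- It names a different method from the preceding sentence without saying whether the GEE and robust standard errors carry over.
- It applies to the analyses without restriction, yet names only a linear model, although BP control is a yes/no outcome.
- It gives age as an example of a variable to be adjusted for if imbalanced, when age is already adjusted for in every case.

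At stake are the precision of the treatment estimates and the ability to say in advance which model is primary.

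**Working it through.** The plan gives no figure on this point to reproduce. The checks below size the rule.

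**1. Candidates for the trigger.** The Data collection section and Table 1 name these patient characteristics: age, gender, race/ethnicity, social support, education, income, health literacy, zip code, insurance status, diabetes, hypertension, cardiovascular disease, food insecurity and preferred language. That is 14. Age and preferred language are already in the GEE, which leaves 12.

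**2. Chance of at least one trigger under correct randomisation.** The formula is 1 - 0.95^k, assuming a 5% level (the plan states none for these tests) and independent tests.

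| Candidate list | k | Chance |
|---|---|---|
| All named characteristics not already in the model | 12 | 1 - 0.540 = 46% |
| Age and diabetes only, as bracketed | 2 | 1 - 0.9025 = 10% |
| Diabetes only, as age is already in the model | 1 | 5% |

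The figures are for one comparison of two groups. Several of the 12, such as income, education and insurance, are probably correlated, so 46% is towards the high end.

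**3. Effect of the trigger on type I error.** Simulation: 200 patients per group, one covariate, no clustering, 20,000 trials per setting. The Monte Carlo standard error is √(0.05 × 0.95 / 20,000) ≈ 0.0015.

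| Correlation of covariate with outcome (assumed) | Never adjust | Adjust if significant | Always adjust |
|---|---|---|---|
| 0.3 | 0.050 | 0.046 | 0.053 |
| 0.5 | 0.049 | 0.041 | 0.051 |

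The conditional rule falls below 5%, so it is mildly conservative. Where the covariate is not flagged, its large imbalances have been removed, but the unadjusted standard error still allows for them.

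**4. Precision forgone.** Always adjusting for a covariate with correlation r to the outcome reduces residual variance to 1 - r² of its value: 1 - 0.09 = 0.91 for r = 0.3 and 1 - 0.25 = 0.75 for r = 0.5. The standard error falls by 1 - √0.91 ≈ 5% and 1 - √0.75 ≈ 13%. With a single covariate, the conditional rule obtains this gain in only about 5% of trials. The correlations are assumptions, because the documents give none.

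**5. If the clustering correction were dropped.** The design effect is 1 + (m - 1) × ICC, and the actual type I error is 2 × [1 - Φ(1.96/√design effect)]. The cluster size m is assumed to range from 2 to 40.

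| ICC | Design effect | Type I error |
|---|---|---|
| 0.0008 (Sample size considerations) | 1.001 to 1.031 | 0.050 to 0.054 |
| 0.01 (assumed) | 1.01 to 1.39 | 0.051 to 0.096 |

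The stated ICC is for systolic BP across providers. The registry is randomised by practice team, and no team-level ICC is given.

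**The case against.** The strongest defence is that the plan is largely pre-specified. Three covariates enter whatever the balance, and the trigger concerns additions only. This stands: a reader might infer that all adjustment depends on baseline tests, and the text does not support that.

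A reader might also infer that a trigger replaces the GEE by ordinary regression and so loses the clustering correction. The article does not say so. The analyses to be adjusted are those just described, and adding covariates to that GEE is at least as natural a reading. The defect is ambiguity. At the stated ICC even the worse reading changes type I error little, although the team-level value is unknown.

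On the binary outcome, a GEE can handle BP control, so the main model is not at fault. Link functions are commonly left to an analysis plan, and the sample size section treats systolic BP as the main outcome. That narrows the point to the conditional step. There the article does name a method, and it is not the usual one for a proportion.

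Two further inferences fail. The rule does not inflate alpha, as check 3 shows. Nor does it change the estimand for systolic BP, because adjusted and unadjusted linear models target the same mean difference. Only some binary effect measures, such as the odds ratio, change with the covariate set.

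Finally, the Data collection section plans a comparison of baseline characteristics but mentions no test. The fault lies in the Data analysis rule alone.

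**Conclusion.** The point holds in a limited form. The article states a rule that picks additional covariates by chance imbalance, does not say whether the clustered GEE is kept, names a linear model for a step that includes a binary primary outcome, and lists age twice. Because the rule is stated, this is not a matter merely left to an analysis plan.

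The chance that it alters the model ranges from about 5% to about 46%, depending on how long the candidate list is, with a 5% level and independent tests assumed. The harm is lost precision (roughly 5% to 13% in the standard error for one covariate with an assumed correlation of 0.3 to 0.5) and a primary model that is not settled beforehand. It is not a false-positive problem.

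**What to change.** Delete the significance trigger. Pre-specify baseline systolic BP and diabetes status alongside age, clinic and preferred language, and include all of them whatever the observed balance, in the same clustered GEE with robust standard errors. State an identity link for systolic BP and a binomial model with a logit or log link for BP control.

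Say how baseline systolic BP is handled. If the 12-month value or the change is the outcome, enter baseline as a covariate. If baseline is modelled as one of the repeated outcomes, handle it through that model and not also as a covariate.

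Label any adjustment for observed imbalance as a sensitivity analysis in the same model.

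The cost is a change of wording. Table 1 shows that blood pressure and co-morbid conditions are already collected at baseline.

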## Discussion

Despite scientific advances that can delay CKD decline and decrease CKD-associated morbidity and mortality, and incorporation of these advances into national [43] and international [44] guidelines, delivery of guideline concordant CKD care remains elusive for many kidney disease patients [45, 46]. This is particularly true among patients who receive care in safety-net settings, where translation of evidence into practice is often impeded by low patient awareness of CKD, poor patient engagement in care, competing clinical demands, and an inefficient health care delivery system [47].

Patient self-management support is an important component of chronic care management, yet many primary care practices do not consistently provide this support due to limitations of training, time, and resources. Linguistically and culturally concordant health coaches are an untapped resource to provide this support, as demonstrated by a recent study that demonstrated improved BP, glycemic and lipid control among low-income, hypertensive, diabetic or hyperlipidemic patients working with medical assistant health coaches [48]. The KARE study tests the impact of a comprehensive CKD self-management support program that occurs outside of the primary care encounter and employs accessible technology and lay health coaches to enhance patient awareness of CKD and engagement with care.

Supporting providers in their delivery of CKD-care is key to maximizing the clinical benefits of patient health coaching. The KARE study will test the effectiveness of a primary care electronic CKD registry with elements of point-of-care decision support and out-of-care population health, to empower non-physician practice team members to participate in the delivery of guideline concordant care.

We hypothesize that patients who receive ATSM and health coaching, and whose practice teams are randomized to the registry, will show significant improvement in systolic BP, reduction in albuminuria, and achieve higher self-efficacy for CKD self-management. If KARE interventions are indeed effective at improving health outcomes among safety-net patients with CKD, the identification of feasible and sustainable characteristics will facilitate their dissemination to other delivery systems across the United States, advancing the goal of healthy equity for people with CKD.

## Abbreviations

CKD: Chronic kidney disease
KARE: Kidney Awareness Registry and Education
BP: Blood pressure
ACEi: Angiotensin converting enzyme inhibitor
ARB: Angiotensin receptor blocker
ATSM: Automated telephone self-management
EMR: Electronic medical record
eGFR: Estimated glomerular filtration rate
PEM: Patient educational material
